### Secondary End Point Analysis

The secondary end points were to identify clinical (comorbidities, presence of pain, tumor type, type of treatment), psychological (personality traits, anxiety, depression, self-efficacy for coping with cancer, sense of coherence, and risk perception), and QoL variables predicting patients’ adherence to OATs. These variables are used as predictors for evaluating nonadherence to OATs among patients with MBC and for enriching the preliminary version of a machine learning model developed in the retrospective study. Our initial machine learning models that are evaluated as an intervention in this study were built based on variables extracted from clinical notes by using natural language processing. Once the data collection for this study is complete, we will also use the data collected to improve our initial machine learning models. Data for the secondary end points are collected using the European Organization for Research and Treatment of Cancer QoL Questionnaire Core 30 (EORTC-QLQ-C30) [33,34], European Organization for Research and Treatment of Cancer QoL 23-item Breast Cancer-specific Questionnaire (EORTC-QLQ-BR23) [35], and the Brief Pain Inventory (BPI) [36]. To evaluate psychological variables, we used the State-Trait Anxiety Inventory (STAI-Y) [37,38], Beck Depression Inventory-II (BDI-II) [39,40], Big Five Inventory (BFI) [41], Brief Italian version of Cancer Behavior Inventory (CBI-B/I) [42,43], 13-item Sense of Coherence scale (SOC-13) [44], and risk perception (using 2 visual analogue scales) [45,46].

### Study Design

#### Treatment Adherence DSS

The first version of the web-based DSS, namely, TREAT (treatment adherence support) was designed and developed in the first year of the Pfizer Project (65080791) by using a patient-driven approach. The development phase was systematized in 5 steps. First, a systematic review of the literature was conducted to explore the main issues related to the interventions fostering adherence in patients with breast cancer [47]. Second, 4 focus group studies with 19 patients with MBC (mean age [years] 55.95, SD 6.87; range 46-70) with different metastasis localizations were implemented in order to explore patients’ unmet needs related to the MBC disease and knowledge about the adherence, barriers, roadblocks, and resources related to OATs and to examine the role of technologies and decision support as aids fostering adherence behaviors during the care pathway [45]. The first and second steps informed the third step in which a preliminary set of mock-ups of TREAT using Wikimedia technology was shaped. TREAT was developed as a web-based application accessible by patients through a web link, without personal registration, and in Italian according to the patient’s user approach. The information contained in TREAT was constructed using the international guidelines for patients with MBC (eg, European School of Oncology-European Society for Medical Oncology 2nd international consensus guidelines for advanced breast cancer) [1,46]. Further, the information was organized using different setups (written text, figures, flowcharts, graphs, and tables). In the fourth step, this preliminary version was revised by an internal and multidisciplinary review group (oncologists, psychologists, technicians, and patients). Finally, the TREAT’s revised version was translated and published.

Currently, TREAT is organized into 4 key sections. Section A on metastatic breast cancer provides information on MBC disease (eg, definition, clinical management), physical consequences (eg, pain, weight loss, lack of energy), psychological consequences (eg, anxiety, depression, fatigue), anticancer treatments and the associated side effects, and benefits that can be experienced during the care pathway. Section B on adherence to cancer therapies discusses the meaning of nonadherence and its consequences, incidence in the population with cancer, and determinants of medication adherence according to the World Health Organization’s approach. Section C on promoting adherence provides information about the resources (eg, personal beliefs, social support, trust in the health care providers), barriers (eg, distress, inadequate knowledge) of medication adherence, and the different available interventions (eg, educational, affective, behavioral) to promote patients’ adherence. Further, TREAT delivers specific self-managed suggestions to mitigate potential risk factors associated with nonadherence and an example of a specific training based on a goal-setting approach. In Section D, that is, My Adherence Diary, patients are invited to write a free-text diary reporting doubts, concerns, thoughts, and behaviors related to their disease and therapies, sharing this information with their oncologists in the following clinical consultation (Figures 1-2).

**Figure 1 figure1:**
[figure not shown]
The 4 main sections of the decision support system in Italian. Section A: metastatic breast cancer; Section B: adherence to cancer therapies; Section C: promoting adherence; Section D: my adherence diary. The screenshot with the decision support system, namely, “TREAT - Supporting Therapy Adherence” is shown in the center.

**Figure 2 figure2:**
[figure not shown]
Screenshots of the decision support system, exemplifying some examples of the information nested in different sections of the system (A, B, C, D). A. “The Section on Pills” refers to a short summary enclosed at the end of each section of the decision support system reporting the key themes (renamed pills) discussed in the section. B. “Resources” is a flowchart on the main resources that can improve medication adherence. C. “Benefits and side effects of the treatments” is a table that shows the action of each anticancer treatment, type of drug, expected benefits, and side effects. D. “The adherence dimension” is a written text that informs about the dimension of nonadherence in the population with cancer.

We also developed a machine learning application, which will be tested with the DSS. This application focuses on models to predict adherence risk factors and used data extracted from the electronic health records of the IEO. Specifically, the machine learning models focused on 2 outcomes: short-term and long-term side effects as well as physical status and comorbid conditions. We evaluated the models predicting performance by utilizing metrics such as area under the curve, precision, recall, sensitivity, specificity, κ, and positive and negative predictive values. Based on these criteria, we identified the top performing models, which were integrated into a web application built using the Shiny open source framework for the R statistical language (R Core Team) [48]. We designed this application for shared decision-making sessions between patients and oncologists. It also uses the Shapley interpretable machine learning algorithm, which offers insights into the specific risk factors that played a role in predicting outcomes for individual patients.

#### Participants

A sample of 100 patients enrolled consecutively in May 2023 in the IEO at the Division of Medical Senology with an MBC diagnosis. The enrollment started in May. Specifically, the observed outcomes of 50 patients with MBC exposed to the DSS (experimental group) and 50 patients with MBC not exposed to the intervention (control group) are evaluated.

#### Inclusion and Exclusion Criteria

The inclusion criteria were female patients with MBC, 18 years of age and older, with a prescription of oral treatment (eg, oral chemotherapy, endocrine therapy, cyclin-dependent kinase 4/6 inhibitors), having internet access and a personal smartphone or tablet, and ability to read and sign informed consent. The exclusion criteria were the presence of any primary psychiatric or neurological conditions.

### Procedure

#### Randomization

Patients who signed the informed consent are given a unique identifier and assigned to either the control or intervention arm in a 1:1 ratio. First, the system asks to confirm all the inclusion and exclusion criteria. Then, an independent researcher generates a random sequence using the statistical language R (R Core Team 2020). Our randomization schedule involves an undisclosed blocking size that the data science team calculates without stratification. A patient is considered randomized when the randomization system assigns the patient an identification number according to a pre-established randomization list. We have created 2 different groups: the experimental group (n=50), in which each participant receives the link for the DSS and is trained to use the DSS for 3 months; and the control group (n=50), in which each patient receives standard care and suggestions bolstering adherence. Among all participants, the personal nonadherence risk is calculated through the preliminary version of the machine learning model to predict patients’ nonadherence behavior. 

#### Recruitment and Follow-Up

Patients admitted to the Division of Medical Senology of the IEO are enrolled by the oncologist during the formal clinical consultation. Patients are enrolled even if they already had oral treatments in the past and they are switching to a new one. The patients who show interest in this research have a phone call with a trained psychologist to receive further information about the Pfizer study. If patients decide to participate in this study, the psychologist plans a consultation to receive informed consent and a preliminary assessment. Patients are informed that TREAT will not replace the clinical consultation. However, it should help manage oral treatment and improve adherence through education using evidence-based information. Patients may decide to discontinue their participation in the trial without any penalties. Patients who refuse to participate in this study are asked to complete a short refusal survey regarding the main reasons for not participating and their demographic information in order to assess the potential differences among the participants. Furthermore, patients have to contact the pertaining division for any necessity. Data are collected by the REDCap (research electronic data capture) platform and stored centrally by the IEO.

### Measures

#### Assessment of Nonadherence to OATs

This study uses the operational definition of adherence provided by the International Society for Pharmacoeconomics and Outcomes Research Medication Compliance and Persistence Work Group, which defines adherence as “the extent to which a patient acts in accordance with the prescribed interval and dose of a dosing regimen” [49]. Coherently, the nonadherence to OATs is evaluated using a prospective method [15] by weekly medication diaries and 2 self-reported measures.

#### Adherence Medication Diary

A weekly paper diary is given to patients to monitor their medication intake. The diary will assess if medications are taken as prescribed and the possible reasons for not taking pills (eg, side effects, forgetfulness, no pill refill). The data collected refer to the number of pills not taken per week and the number of pills established according to the patient medical prescription protocol per week as well as planned interruptions. Further, the diary evaluates and monitors the side effects, their intensity (from 0 to 10) associated with the therapy intake, and their emotions, thoughts, behaviors, and consequences.

#### MMAS-8 Self-Report Questionnaire (© 2006 Donald E Morisky)

The MMAS-8 scale [31,50,51] is an 8-item self-report questionnaire evaluating treatment adherence (forgetfulness, medication-taking behavior, adverse effects, and problems) (Cronbach α=.83). The first 7 items have dichotomous responses (0=Yes, 1=No), and the last includes a 5-point Likert scale response [52].

#### AAI Self-Report Questionnaire

The AAI is a 28-item self-report questionnaire on a 5-point Likert scale response (from “does not fit” to “perfect fit”) evaluating treatment adherence (Cronbach α=.80) [32]. The AAI is organized into 4 subscales: cognitive functioning (evaluating the ability to remember issues and tasks related to adherence in the short and long term), patient-provider communication (evaluating thoughts, attitudes, feelings, and ideas related to adherence between patient and medical provider), self-efficacy (evaluating the belief in one’s ability to adhere to medication and a history of similar success), and commitment to adherence (evaluating the determination to overcome obstacles to achieve adherence).

#### Demographic, Clinical, Emotional, and QoL Assessments

Considering that adherence to OATs is explained by a set of mutual and interconnected determinants, a comprehensive pool of self-reported measures is administered to identify the psychological predictors of nonadherence in patients with MBC.

#### Patient Demographic and Clinical Variables

Age, gender, education, marital status, cancer diagnosis and staging, oncological treatments, BMI, alcohol and smoking habits, and comorbid medical disorders are collected through electronic medical records.

#### STAI-Y Self-Report Questionnaire

The STAI-Y is a 40-item self-report questionnaire on a 4-point Likert scale (Cronbach α=.89). The STAI-Y evaluates both trait anxiety (20 items) and state anxiety (20 items) [37,38].

#### BDI-II Self-Report Questionnaire

The BDI-II is a 21-item self-report questionnaire on a 4-point Likert scale response evaluating depression (Cronbach α=.89). The BDI can be administered to adults and adolescents aged 13 years and older [39,40].

#### CBI-B/I Self-Report Questionnaire

The CBI-B/I is a 12-item self-report questionnaire on a 7-point Likert scale response (from not all confident to totally confident) evaluating self-efficacy for coping in patients with cancer (Cronbach α=.84). The CBI-B/I is composed of 4 subscales: coping and stress management, maintaining independence, managing affect, and participating in medical care [42,43].

#### SOC-13 Self-Report Questionnaire

The SOC-13 is a 13-item self-report questionnaire on a 7-point Likert scale response (Cronbach α=.76). The SOC-13 is composed of 3 subscales: comprehensibility, manageability, and meaningfulness [44].

#### BPI Self-Report Questionnaire

The BPI is a 9-item self-report questionnaire evaluating pain intensity during the past 24 hours (Cronbach α=.91) [36].

#### EORTC-QLQ-C30 Self-Report Questionnaire

The EORTC-QLQ-C30 is a self-report questionnaire composed of 28 items on a 4-point Likert-type scale (ranging from not at all to very much) and 2 items, that is, general global health status and QoL on a 7-point Likert-type scale (ranging from very poor to excellent) [33,34]. The EORTC-QLQ-C30 provides information on 3 areas: functional (physical, role, cognitive, emotional, and social), symptoms (appetite loss, fatigue, pain, nausea, constipation-diarrhea, dyspnea, and insomnia), and global health status or QoL (Cronbach α=.85) [32,33]. Further, the EORTC-QLQ-B R23 for patients with breast cancer has been used previously (Cronbach α=.87) [34,35].

#### BFI Self-Report Questionnaire

The BFI is a 44-item self-report questionnaire on a 5-point scale (from disagree strongly to strongly agree) that assesses 5 dimensions of personality: openness to experience (Cronbach α=.78), conscientiousness (Cronbach α=.81), extraversion (Cronbach α=.87), agreeableness (Cronbach α=.81), and neuroticism (Cronbach α=.82) [41].

#### Risk Perception

Risk perception is evaluated using 2 visual analogue scales (from 0 to 100): one for the objective and one for the subjective risk perception. These items were developed using the Weinstein approach [45,46].

### Timeline

There are 3 assessment time points. At the baseline (T0), all patients fill a set of validated measures (MMAS-8, AAI, STAI-Y forms I and II, BDI-II, CBI-B/I, SOC-13, BPI, EORTC-QLQ-C30, EORTC-QLQ-BR23, BFI, and visual analogue scale). The expected time to complete all the given questionnaires at baseline is approximately 40 minutes. Access to DSS is given to the experimental group for 3 months. At T1 and T2, the following questionnaires are filled: MMAS-8, AAI, STAI-Y form I, BDI-II, CBI-B/I, EORTC-QLQ-C30, and EORTC-QLQ-BR23. Further, all patients have to fill a weekly adherence medication diary for 3 months. Variables that are not sensitive to change, for example, personality (BFI) and anxiety traits (STAI-Y form II) are collected only at T0. Each month, all participants receive a brief telephone interview in which they are monitored for adherence to the research protocol. Two psychologists perform the monthly telephone interview to monitor the filling out of the questionnaires and the medication adherence diary supporting patients with MBC in this task, barriers, and concerns related to the study participation. At T3 (3 months), all behavioral and psychological measures are filled, and an interview (online or vis-à-vis) is performed.

### Calculation of Sample Size

The sample size calculation was based on estimates for the effectiveness of TREAT as the primary outcome, assuming that the final analysis would be performed with a 2-sample 2-sided *t* test, a power of 96.4%, an α of .05, a standard deviation of 1.2, and a minimal difference in outcomes of 0.51 (effect size of 0.42) based on the patients’ self-reported satisfaction with the treatment decision [53]. Under these considerations, the final sample size was calculated to be 100 patients with MBC, with 50 individuals per group (50 patients with MBC exposed to DSS and 50 patients with MBC not exposed to the intervention). This sample size is expanded to 120 when a 20% attrition rate is used.

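### The stated power of 96.4% is wrong: 50 per group, difference 0.51 and SD 1.2 give about 56% in the planned two-sample t test

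*Protocol article*

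**What the plan says.** The section Calculation of Sample Size in the protocol article gives a complete set of inputs. The analysis is fixed by "assuming that the final analysis would be performed with a 2-sample 2-sided *t* test". The other inputs are "a power of 96.4%, an α of .05, a standard deviation of 1.2, and a minimal difference in outcomes of 0.51", and the section also prints the standardised value, "effect size of 0.42". It presents the sample size as following from these inputs: "the final sample size was calculated to be 100 patients with MBC, with 50 individuals per group". It then expands the total to 120 for 20% attrition. The Randomization section confirms equal allocation, with patients "assigned to either the control or intervention arm in a 1:1 ratio". The difference and SD are taken from an outside source on patients' satisfaction with the treatment decision. No section gives a correlation, a variance reduction or a different test for this calculation.

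**The concern.** Test, sidedness, alpha, SD, difference and group size are all stated, so the power can be computed with no further assumption. A power above 96% for an effect of a little over 0.4 SD with only 50 per group is implausible on sight, since that combination usually sits not far above a coin toss.

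The error affects how the result will be read. A power of 96.4% means a type II error of 100 − 96.4 = 3.6%, and a reader who trusts it would take a non-significant comparison as strong evidence that the decision support system does not produce the minimal difference. If the true power is near 56%, the same result says little.

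**Working it through.** **Inputs** (all from Calculation of Sample Size, with 1:1 allocation from Randomization)

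- Two-sample t test, two-sided, alpha = 0.05
- SD σ = 1.2
- Difference δ = 0.51
- n = 50 per group
- Stated power 96.4%

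**Step 1: are difference, SD and effect size consistent?** d = δ/σ = 0.51/1.2 = 0.425. The printed 0.42 agrees apart from rounding, so these three figures support each other.

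**Step 2: try to reproduce the stated power.** The noncentrality parameter is d × √(n/2) = 0.425 × √25 = 2.125. The degrees of freedom are 2 × 50 − 2 = 98, and the two-sided critical value is 1.984.

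- Exact (noncentral t): P(T > 1.984 given noncentrality 2.125) = 0.557. The opposite tail adds a negligible amount.
- Normal approximation: Φ(2.125 − 1.960) = Φ(0.165) = 0.566.
- Simulation, 50,000 trials: 0.558.
- Exact with d rounded to 0.42: 0.548.

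The stated 96.4% is not reproduced. The gap is 96.4 − 55.7 = 40.7 percentage points, far too large for rounding or a choice of software.

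**Step 3: what would 96.4% need?** By the normal approximation, n per group = 2(1.960 + 1.799)²/0.425² ≈ 156.5, so 157. The exact t calculation gives 157.4, so 158 per group, about 315 in total (about 162 per group with d = 0.42). With n held at 50 per group, the effect would have to be d = 0.76, which means a difference of 0.91 at SD 1.2, or an SD of 0.67 at difference 0.51. For 80% power the exact calculation gives 87.9, so 88 per group.

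**Step 4: do other readings rescue the figure?** Power at d = 0.425, exact t unless noted:

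| Reading | Power |
|---|---|
| 50 per group, one-sided | 67.9% |
| 60 per group (all 120 patients), two-sided | 63.6% |
| 100 per group, two-sided | 84.9% |
| 120 per group, two-sided | 90.6% |
| 120 per group, one-sided | 94.9% |
| 1.2 read as a variance, 50 per group | 63.5% |
| Baseline-adjusted, assumed correlation 0.5 (normal approximation) | 68.9% |
| Baseline-adjusted, assumed correlation 0.8 (normal approximation) | 94.3% |

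None gives 96.4%. Those that come nearest depart from the stated sidedness and group size, or rely on a correlation that the document does not give.

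**Step 5: a possible origin.** A two-sided one-sample or paired t test with 80 observations at d = 0.425 gives 96.37%, which rounds to the printed figure (96.0% at d = 0.42). Selecting the wrong test, with 100 × 0.8 = 80 evaluable patients, would therefore produce it. This is an inference. The document mentions neither a paired test nor 80 patients, and the finding does not depend on it.

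**Step 6: what the design can detect.**

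| Analysed per group | Power at 0.51 | Detectable with 80% power |
|---|---|---|
| 50 | 55.7% | 0.566 SD (0.68 at SD 1.2) |
| 48 (120 enrolled, 20% lost) | 54.0% | 0.578 SD (0.69) |
| 40 (100 enrolled, 20% lost) | 46.7% | 0.634 SD (0.76) |

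**The case against.** The central arithmetic cannot be disputed. What can be argued concerns the points around it.

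- **Attrition.** The 46.7% figure assumes that 100 are enrolled and 80 analysed. The abstract, Participants and Randomization sections support an enrolment of 100, but the sample size section also mentions 120, and 20% loss from 120 leaves 48 per group and 54.0% power. The objection stands as a condition on that figure. Either value is more than 40 points below the stated one.
- **Which number is wrong.** The document does not show whether the power, the effect or the sample size was mis-entered. This stands, although the agreement of 0.51, 1.2 and 0.42 makes a misprint in the difference or the SD less likely. While the stated test, effect and group size remain, the power is about 56%.
- **Scale.** The difference and SD come from satisfaction with the treatment decision, whereas the primary end point is the ratio of pills taken to pills prescribed. The 56% is therefore the power for the assumption as stated, and power for adherence itself cannot be derived from this document. This limits what the corrected figure means but does not defend 96.4%.
- **Reporting.** Results are already to be given with 95% confidence intervals under Generalized Linear Models. Those are described for predicted means, and nothing there says how a null comparison will be interpreted.

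**Conclusion.** The concern holds. For the stated test, alpha, difference, SD and group size, the power is 55.7% (54.8% with the rounded effect), not 96.4%. The chance of missing the stated minimal difference is 100 − 55.7 = about 44%, some twelve times the implied 3.6% (44.3/3.6 ≈ 12.3). Reaching the stated power would take about three times the planned number of patients (315 against 100).

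The conclusion takes the inputs as printed, complete data on 50 per group, and an unadjusted t test as the section specifies. Attrition lowers the power further, to between 47% and 54% depending on whether 100 or 120 are enrolled. Baseline adjustment could raise it, but the document gives no correlation from which to credit that. The contradiction lies within one paragraph that states both inputs and result, so it is not a detail left to a fuller document. It must be corrected.

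**What to change.** In Calculation of Sample Size, replace the stated power with what the inputs give: about 56% with 100 patients analysed, and about 47% if 100 are enrolled and 80 analysed (about 54% if 120 are enrolled and 20% are lost). State the difference detectable with 80% power at 50 per group, 0.57 SD or 0.68 on the scale with SD 1.2. Add a sentence that a non-significant result will be reported through the 95% confidence interval of the group difference and described as inconclusive, not as evidence of no effect.

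Before making the change, the sponsor should check the original calculation. If the difference or SD was misreported, the power should be recomputed from the verified values and both shown.

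The cost is a wording correction and a less favourable stated power. No added patients are needed to make the text correct. Keeping a target of 96.4% for this difference would be a separate decision, at about 158 per group.

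Suggested wording: *With 50 patients analysed per group, a two-sided two-sample t test at alpha 0.05 has about 56% power for a difference of 0.51 (SD 1.2) and 80% power for a difference of 0.68. With 40 analysed per group, the power for 0.51 is about 47%. A non-significant result will be interpreted through its 95% confidence interval and not taken as evidence of no effect.*

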## Methods

### Primary End Point Analysis

The primary end point was to assess the effectiveness of the DSS web-based solution and the machine learning web application in promoting adherence to OATs in a sample of 100 patients with MBC at 3 months. The adherence is evaluated using the number of pills taken divided by the number of pills prescribed. Further, the adherence is assessed using behavioral measures: the 8-item Morisky Medication Adherence Scale (MMAS-8) [31] and Adherence Attitude Inventory (AAI) [32].

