### Limitations of This Trial

Despite the key contributions of this study in the field of the medication adherence to OATs among patients with MBC, some limitations have to be acknowledged. First, the questionnaires used to refine our risk-predictive model might cause cognitive burden and general fatigue among participants. However, a monthly telephone interview has been introduced as a mitigation risk strategy. The interview is aimed to support participants in filling out the questionnaires and medication adherence diary and to manage barriers and concerns related to this study. Related to this aspect, the second limitation concerns the recall bias that might be generated using self-report measures. Further, self-report measures might overvalue adherence compared to the other prospective methods such as the Medication Event Monitoring System. However, the weekly medication diary method, in which patients have to report a detailed and systematic description of pill counts, side effects, and barriers related to the management of the therapy and missed doses, can aid in providing a more comprehensive picture of medication adherence. Moreover, as highlighted by Shah and colleagues [15], the diary has a higher accuracy and minor recall bias and permits the evaluation of subjective information (eg, emotions, thoughts, worries, behaviors, expectations) related to the medication coherently with the processual model of the adherence used in this research protocol [8]. Third, a monthly follow-up and a 3-month end point have been established, considering the type of diagnosis, high variation in the prognosis, and shifting in the lines of treatment due to cancer progression or declining physical functioning. This short end point might affect a deep understanding of the efficacy of our DSS in the long term. However, previous studies have used correspondent follow-ups and end points [13]. Fourth, as observed by other studies on patients with MBC [14], an additional risk that should be considered is related to the overestimated adherence rate. Patients participating in clinical trials are highly motivated, possibly leading to greater adherence to the OATs prescribed. Fifth, the initial version of the machine learning web application was not able to directly predict patient adherence. Instead, it predicted adherence risk factors, including short-term and long-term side effects, as well as physical status and comorbid conditions. This is a limitation of the data we used to build this initial version of the model, as it was not possible to reliably identify adherence patterns. However, predicting adherence risk factors can still provide insights that can assist in improving OAT adherence during shared decision-making sessions between physicians and patients.

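### The stated 96.4% power rests on figures for satisfaction with a treatment decision, so it does not apply to adherence, the primary outcome

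*Protocol article*

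**What the plan says.** Calculation of Sample Size opens: "The sample size calculation was based on estimates for the effectiveness of TREAT as the primary outcome". It assumes a two-sample, two-sided t test with alpha .05, power 96.4%, SD 1.2 and a difference of 0.51 (effect size 0.42). It attributes these to patients' "self-reported satisfaction with the treatment decision" in a cited source. The result is 100 patients, 50 per group, expanded to 120 for 20% attrition.

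Primary End Point Analysis defines something else, adherence to oral anticancer treatment at 3 months: "The adherence is evaluated using the number of pills taken divided by the number of pills prescribed". The MMAS-8 and AAI are added under the same end point.

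Timeline lists what is collected:
- Baseline: "MMAS-8, AAI, STAI-Y forms I and II, BDI-II, CBI-B/I, SOC-13, BPI, EORTC-QLQ-C30, EORTC-QLQ-BR23, BFI, and visual analogue scale".
- T1 and T2: "MMAS-8, AAI, STAI-Y form I, BDI-II, CBI-B/I, EORTC-QLQ-C30, and EORTC-QLQ-BR23".
- Month 3: "At T3 (3 months), all behavioral and psychological measures are filled, and an interview (online or vis-à-vis) is performed".

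Weekly medication diaries run throughout.

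**The concern.** The power statement is labelled as being for the primary outcome, but its inputs describe a different construct. Being satisfied with a decision is not the same as taking the pills. The article names no satisfaction scale as something it will collect or analyse, so the sample size is justified on a variable outside the trial's own outcomes.

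What is at stake is how the result is read. A null result on adherence could be taken as good evidence that TREAT does not work, on the strength of a 96.4% power figure that was never about adherence. The trial states no power or precision for its primary question.

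**Working it through.** **1. The plan's own figure.** Inputs from Calculation of Sample Size: difference 0.51, SD 1.2, 50 per group, two-sided alpha .05.

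- Standardized effect: 0.51 / 1.2 = 0.425 (stated as 0.42).
- Noncentrality: 0.425 × √(50/2) = 2.125.
- Normal approximation: Φ(2.125 − 1.96) = Φ(0.165) = 56.6%. Noncentral t: 55.7%.
- With 0.42 instead: noncentrality 2.10, normal 55.6%, noncentral t 54.8%.
- With 60 per group, noncentral t: 62.6% (0.42) to 63.6% (0.425).

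The stated 96.4% is not reproduced. By normal approximation it would need n per group = 2 × ((1.960 + 1.799) / 0.425)² = 156.5, so 157 (158 by t test).

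**2. Where satisfaction appears.**

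| Section | Content | Decision satisfaction? |
|---|---|---|
| Primary End Point Analysis | pill ratio, MMAS-8, AAI | no |
| Secondary End Point Analysis | clinical, psychological and quality of life predictors | no |
| Measures | diary and named questionnaires | no |
| Timeline | the same set; month-3 interview of unstated content | not named |
| Generalized Linear Models | pills taken and the listed scales | no |

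It appears only as the source of the sample size inputs.

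**3. Can 0.51 and 1.2 be on the pill-ratio scale?** The diary records pills not taken and pills prescribed, so the ratio is 1 − (not taken / prescribed) and lies between 0 and 1. The largest SD possible for a variable confined to 0-1 is 0.5, with half the values at each end. An SD of 1.2 is impossible there, and a difference of 0.51 would be half the full range. The MMAS-8 and AAI are multi-point scales on which such numbers are not impossible, but the article does not attribute them to either.

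**4. What the planned n can say about adherence.** No SD is given, so only the standardized figure is free of assumptions. By noncentral t, two-sided .05, 80% power:

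- 50 per arm: 0.566 SD.
- 48 per arm (120 × 0.80 = 96, halved): 0.578 SD.
- 60 per arm: 0.516 SD.

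Multiplied by an assumed pill-ratio SD (illustration only):

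| Assumed SD | 50 per arm | 48 per arm | 60 per arm |
|---|---|---|---|
| 0.10 | 0.057 | 0.058 | 0.052 |
| 0.15 | 0.085 | 0.087 | 0.077 |
| 0.20 | 0.113 | 0.116 | 0.103 |

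At 50 per arm, power for a true difference of 0.10 (normal approximation) would be 99.9%, 91.5% and 70.5% at SDs of 0.10, 0.15 and 0.20. The answer turns on an SD that the article does not state.

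**The case against.** The best defence is that 0.42 is a standardized effect, so it is free of scale and could be proposed for adherence whatever its source. That is possible in principle, but the article neither says so nor gives a reason to expect the same standardized effect on pill-taking as on satisfaction. Nor does it rescue the claim, because step 1 gives about 55-56% power at 50 per arm.

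A second defence is that the content of the month-3 interview is not described, so satisfaction might be asked there. Even so, it is named nowhere as an outcome, and power for it would not be power for adherence.

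Third, this is a fault in the justification. Correcting it changes neither the design nor the analysis, and results will carry 95% confidence intervals in any case. That stands, and it is why the fix is small. It does not make the stated power right.

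A reader might go further and infer that adherence will sit so close to its maximum that no detectable gain is possible. The documents do not support this. Limitations of This Trial says only that "an additional risk that should be considered is related to the overestimated adherence rate", a possibility with no adherence level and no ceiling mentioned. The Introduction cites tamoxifen nonadherence of 30% to 85% in this population, which points the other way. Any headroom calculation would need an invented control mean. It could not keep a common SD either, because an arm whose mean ratio reached 1 would have an SD of zero.

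**Conclusion.** The concern holds. The 96.4% power is presented as power for the primary outcome, but its inputs belong to a variable that is not an end point, a listed measure or a modelled outcome, and they cannot be on the pill-ratio scale. No power is established for adherence. This rests on the article's text alone and needs no assumption.

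Its size can be given only conditionally. If 0.42 is carried over, power is about 55-56% at 50 per arm (about 63-64% at 60). If the pill-ratio SD is assumed to be 0.10-0.20, the difference detectable with 80% power at 50 per arm is 0.057-0.113. It does not follow that the trial is underpowered for adherence: with a small SD and a difference of 0.10 it would be well powered. The article gives no way to tell.

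**What to change.** Rewrite the paragraph in Calculation of Sample Size:

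- Remove 0.51, 1.2 and 96.4% as the basis for the primary outcome.
- Keep the planned n and state what it can detect for the 3-month pill ratio: 0.57 SD at 80% power with 50 per arm, with a table over a stated range of SDs marked as assumed. Say which number per arm is meant, since this section also gives 120 in total.
- Estimate the SD from the diary data pooled over both arms as they accrue, without arm labels, and restate the precision from it. No arm comparison is made, so no alpha is spent.
- If 0.42 is to be kept as a target for adherence, justify it on adherence grounds and give the power that follows from it.

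The cost is one paragraph and one blinded SD calculation. The stated power or precision will look less favourable than 96.4%.
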